### Sample size

The uniqueness of our research does not make it possible to determine the exact expected effect size. Thus, we decided to follow a proof-of-concept study logic with a pragmatic approach to setting our sample size. A feasibility analysis led us to the conclusion that we could reach a sample of 130 participants in 10 months. We next measured the sensitivity of our experimental design on this expected recruitment rate with Gpower [54] based on the following values: alpha corrected for 2 primary outcomes equal to 0.025, power equal to 0.80, experimental design corresponding to a mixed analysis of variance with repeated measures and an intergroup variable, with an intra-subject correlation of 0.5. Results from the sensitivity analysis show that our experimental design will be able to detect small effect sizes (interaction effect in a mixed anova) of f = 0.137.

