#### Primary outcome analysis

Primary outcome will be first analyzed on an intention-to-treat (ITT) basis, including all patients as originally allocated after randomisation. For missing information due to patient drop-out, we will rely on the linear mixed model and consider the baseline data as part of the outcome matrix. We will also perform a per-protocol (PP) sensitivity analysis including only those patients who completed the treatment originally allocated.

Analyses should be considered as hypotheses generating. To explore the effects of the intervention type on the two primary outcome measures, the results will be compared using linear mixed models. More precisely, the moment of the measure (baseline and immediate follow-up), the intervention (nested within the centers), the centers and the interaction of these factors will be considered as fixed factors. A nested random intercepts and slopes for each participant within the centers will be implemented. Age groups, educational level, objective Z-score (Z-score from 0 to -0.50; -0.51 to -1, etc.) and gender will also be included in the model as stratification factors. Following the linear mixed model, linear contrast will be performed between the two levels of the intervention variable on the first follow-up measure (T1) to explicitly compare the potential benefit of the intervention. Bonferroni adjustment will be performed to correct for multiple testing, more precisely 2 tests (the number of primary measures), and p-value < 0.025 will be considered as statistically significant. 95% CI and standardized effect sizes (SES) from the null model will be calculated. The following convention will be used to interpret effect size: small 0.2–0.49, moderate 0.5–0.79, large ≥ 0.8. As a Proof-of-Concept (POC) study, estimation will be focused on ES but will include p-values as help in interpreting the data.

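### Fixed Bonferroni at 0.025 for BRIEF and MMQ is valid, but Holm's procedure keeps the same 5% family-wise limit and is never less powerful: an optional, low-severity improvement

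*Protocol article*

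**What the plan says.** The primary outcome is measured with two questionnaires, BRIEF and MMQ (Protocol article, Primary outcome). Under Primary outcome analysis, each is analysed with a linear mixed model and a contrast between arms at the first follow-up. On multiplicity the text states "Bonferroni adjustment will be performed to correct for multiple testing, more precisely 2 tests (the number of primary measures" and then "p-value < 0.025 will be considered as statistically significant". No sequential or step-down rule is mentioned.

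The Sample size section uses the same level, "alpha corrected for 2 primary outcomes equal to 0.025", with "power equal to 0.80". It reports that 130 participants suffice to "detect small effect sizes (interaction effect in a mixed anova) of f = 0.137".

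Primary outcome analysis also describes the analyses as hypothesis generating. It puts the emphasis on effect sizes, with p-values as an aid, and plans 95% confidence intervals.

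**The concern.** With two primary tests and a family-wise limit of 5%, fixed Bonferroni is not the most powerful simple rule. Holm's procedure tests the smaller p-value at 0.025 and, only if that is significant, tests the larger at 0.05. The two rules differ in one situation: one questionnaire has p < 0.025 and the other has a p-value from 0.025 up to 0.05. The plan would call the second result non-significant, although 5% family-wise control does not require it and the planned 95% interval for that contrast would exclude zero.

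What is at stake is the chance of a significant result on the second questionnaire, and hence on both. The sample size was set by feasibility, so extra power is more readily found in the analysis rule than in recruitment.

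**Working it through.** **Inputs from the Protocol article.** N = 130, 1:1, so 65 per arm (Trial design; Sample size). Alpha 0.025 per questionnaire and power 0.80 (Sample size). Design: "experimental design corresponding to a mixed analysis of variance with repeated measures and an intergroup variable", "with an intra-subject correlation of 0.5". Two measurement times, baseline and immediate follow-up (Primary outcome analysis).

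**Assumptions.** The correlation r between the BRIEF and MMQ test statistics is not given, so 0 to 0.9 is shown. The true effect is set at f = 0.137 on both scales unless stated otherwise. Tests are taken as two-sided; the sidedness of the primary contrast is not stated separately.

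**1. The plan's own figure.** For the within-between interaction, λ = f² × N × m / (1 − ρ), with m = 2 measurements and 1 and 128 degrees of freedom. At f = 0.137, λ = 0.018769 × 130 × 2 / 0.5 = 9.76, and √λ = 3.124.
- At alpha 0.025 the smallest f with 80% power is 0.1365, which rounds to the stated 0.137. Power at f = 0.137 is 80.3%.
- At alpha 0.05, the level Holm allows at its second step, power at f = 0.137 is 87.3%.

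**2. Hand check at r = 0.** The chance that a p-value falls between 0.025 and 0.05 is 0.873 − 0.803 = 0.070.
- Per questionnaire under Holm: 0.803 + 0.803 × 0.070 = 0.859.
- Both, Bonferroni: 0.803² = 0.645.
- Both, Holm: 0.645 + 2 × 0.803 × 0.070 = 0.757.
- At least one, either rule: 1 − 0.197² = 0.961.

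**3. Simulation over r.** 1,000,000 pairs of t statistics (128 df, non-centrality 3.124 on each). The single-test Bonferroni power is the exact 80.3% throughout.

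| r | Per questionnaire, Bonferroni → Holm | Both, Bonferroni → Holm | At least one, either rule |
|---|---|---|---|
| 0 | 80.3% → 85.9% | 64.4% → 75.7% | 96.1% |
| 0.3 | 80.3% → 85.4% | 67.0% → 77.2% | 93.6% |
| 0.5 | 80.3% → 84.9% | 69.0% → 78.3% | 91.6% |
| 0.7 | 80.3% → 84.4% | 71.4% → 79.8% | 89.1% |
| 0.9 | 80.3% → 83.7% | 74.9% → 81.8% | 85.7% |

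The gain is 3.4 to 5.6 points per questionnaire and about 7 to 11 points for both.

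**4. Unequal effects.** If the second scale has half the non-centrality (1.56), its power rises from 24.3% to 32.2% at r = 0, and from 24.4% to 33.2% at r = 0.5. If the second scale has no effect, power on the first moves from 80.3% to at most 80.5%.

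**5. Error control.**
- No effect on either scale: the chance of any rejection is identical under the two rules (4.94% at r = 0, 4.67% at r = 0.5, 4.34% at r = 0.7).
- A real effect on one scale only: the false-positive rate on the other rises from 2.5% to 4.5% at r = 0, 4.3% at r = 0.5 and 3.8% at r = 0.9. It cannot exceed 5%, because Holm never rejects a p-value of 0.05 or more.

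**The case against.** Nothing in the document is wrong or contradictory on this point. Bonferroni for two tests is valid and prespecified, and the sample-size and analysis sections agree. The trial is presented as hypothesis generating with the focus on effect sizes, so a second p-value between 0.025 and 0.05 would still be reported with its estimate and interval; only its label would change. The gain needs a real effect on both scales, and its size depends on a correlation and effects that the document does not give. All of this stands, and it makes the point one of efficiency and low severity.

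A reader might infer three stronger things that the documents do not support:
- **That Bonferroni buys nothing over Holm.** This is true of the family-wise limit, which is the plan's stated reason for adjusting. It is not true of the error rate on a single null scale when the other effect is real, which is lower under Bonferroni (2.5% against about 4–4.5%). Participants are unblinded and the outcomes self-reported, so this trade deserves mention.
- **That the trial has little power to spare.** The Sample size section says no expected effect could be fixed. The figure f = 0.137 is a sensitivity result at a feasible N, so there is no target against which to judge a margin.
- **That success requires both questionnaires.** No section says so, and power for at least one is the same under either rule.

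The objection does not remove the dominance. The plan does declare a significance cutoff, and Holm meets the same family-wise limit with equal or greater power. The usual defence of Bonferroni, that it comes with simple matching 97.5% intervals, is not used here because 95% intervals are planned.

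**Conclusion.** The point holds as an optional refinement of low severity. The fixed 0.025 rule is correct but less efficient than Holm at the same 5% family-wise limit. With f = 0.137 true on both scales and a correlation from 0 to 0.9, the plan gives up about 3 to 6 points of power per questionnaire and about 7 to 11 points for significance on both. It gives up nothing on the chance of at least one significant result, and almost nothing if only one scale responds. The stated f = 0.137 is unaffected, since Holm's first step is also at 0.025.

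**What to change.** Under Primary outcome analysis, replace the Bonferroni sentence with: *Holm's procedure at family-wise 5%: the smaller of the two p-values is tested at 0.025; if significant, the larger is tested at 0.05.* Keep the planned 95% confidence intervals and label them as unadjusted for multiplicity. Leave the Sample size section unchanged; its alpha of 0.025 then describes Holm's first step.

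Settle the change before any unblinded analysis. It needs no extra participants, data or modelling. The statistical cost is the higher error rate on a null scale when the other effect is real, still within 5%. The administrative cost depends on the route. A protocol amendment needs discussion in the management and steering groups and approval by the funder and ethics committee, with enrolment already under way. An entry in the statistical analysis plan, which is not shown here, would probably be lighter.

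### The primary effect size and its CI are assigned to an undefined null model, and the 95% level does not match the 0.025 test

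*Protocol article*

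**What the plan says.** All of the following is in the protocol article.

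- **Primary outcome analysis, model and contrast.** A linear mixed model is fitted with time point, intervention, centre and their interaction as fixed factors. The time factor is "the moment of the measure (baseline and immediate follow-up"). A linear contrast then compares the two arms at the first follow-up (T1).
- **Primary outcome analysis, test.** There are two primary measures with a Bonferroni correction, so "p-value < 0.025 will be considered as statistically significant".
- **Primary outcome analysis, estimate.** The next sentence reads "95% CI and standardized effect sizes (SES) from the null model will be calculated". The term null model is not defined anywhere in the article. Bands follow for reading the effect size: 0.2 to 0.49 small, 0.5 to 0.79 moderate, 0.8 and above large.
- **Primary outcome analysis, emphasis.** The section gives the analyses exploratory status and says that "estimation will be focused on ES but will include p-values as help in interpreting the data".
- **Secondary outcome analysis.** Intervention effect sizes for the other outcomes come from mixed models of the same kind as the primary one, which do contain the intervention.
- **Sample size.** The sensitivity calculation uses "alpha corrected for 2 primary outcomes equal to 0.025, power equal to 0.80" and a "mixed analysis of variance with repeated measures and an intergroup variable, with an intra-subject correlation of 0.5".

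**The concern.** The effect size is the result this trial puts first, and the sentence saying where it comes from points to a model that, by the usual meaning of the term, cannot supply it. It names one source for the primary effect size, while the preceding contrast and the secondary outcome section imply another.

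A kinder reading is that only the denominator comes from the null model. That leaves open which SD is meant: a random-intercept null model has both a total SD and a residual SD. Either one pools baseline with follow-up scores, so it carries some of the time and treatment effect. Because fixed bands are used to read the result, an estimate near a band limit can change label with the denominator, and a choice not fixed beforehand can be made after the data are seen.

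The CI level is a second, smaller matter. The test is at 0.025 per measure and the interval is at 95%, so the two can point in different directions for the same measure.

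**Working it through.** **1. The plan's own figure.** Inputs from the Sample size section: N = 130, alpha 0.025, power 0.80, correlation 0.5. From the Primary outcome analysis section: two time points. From the design: two arms.

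Noncentrality = f² × N × m / (1 − rho), with m = 2 time points and 1 and 128 degrees of freedom. At f = 0.137 this is 0.01877 × 130 × 2 / 0.5 = 9.76, and power is 0.803. Solving for 0.80 power gives f = 0.1365, so the stated "small effect sizes (interaction effect in a mixed anova) of f = 0.137" reproduces. Alpha 0.05 would have given 0.124, and three time points at alpha 0.025 would have given 0.122. The design therefore rests on the 0.025 level.

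In a 2 × 2 layout f is the between-arm difference in change divided by four total SDs. Hence f = 0.137 means 4 × 0.137 = 0.55 total SD, close to the 0.5 line between the small and moderate bands.

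**2. What a null model can supply.** The model y = intercept + participant effect + error has one fixed coefficient, the overall mean. It has no arm coefficient, so no arm difference and no CI for one. It does supply variance components, which could serve as a denominator.

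**3. Total SD against residual SD.** With correlation rho, residual SD = total SD × √(1 − rho). At rho = 0.5 the effect size is multiplied by 1/√0.5 = 1.414.

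- 0.36 × 1.414 = 0.51
- 0.49 × 1.414 = 0.69

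Estimates of 0.36 to 0.49 (small) would read 0.51 to 0.69 (moderate).

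**4. An illustrative simulation of the denominators.** Assumptions: 20,000 participants, half per arm, true total SD 1, correlation 0.5, a common change of 0.3 SD and a further T1 difference of 0.5 SD. The full-model contrast was 0.503.

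| Denominator | SD | Effect size |
|---|---|---|
| Full-model total SD | 0.996 | 0.51 |
| Null-model total SD | 1.049 | 0.48 |
| Null-model residual SD | √0.677 = 0.823 | 0.503 / 0.823 = 0.61 |

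The two total SDs differ by about 5% (1.049 / 0.996), yet 0.48 and 0.51 fall either side of the 0.5 line. The null model's residual SD raised the result by 1.049 / 0.823 = 1.27 rather than 1.41, because time and treatment effects enter its residual.

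**5. Interval against test.** The normal multiplier is 1.960 for 95% and 2.241 for 97.5%; 2.241 / 1.960 = 1.14.

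For scale, assume a simple unadjusted T1 comparison in SD units with all 65 per arm observed: SE = √(2/65) = 0.175.

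- 95% half-width: 1.960 × 0.175 = 0.344
- 97.5% half-width: 2.241 × 0.175 = 0.393

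Differences between 0.344 and 0.393 give a 95% CI excluding zero and p above 0.025. Example: 0.37 gives p = 0.035, 95% CI 0.03 to 0.71 and 97.5% CI −0.02 to 0.76.

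If a reader used the two 95% intervals as tests, the total error rate could reach 0.05 + 0.05 = 0.10 (1 − 0.95² = 0.0975 if independent). The 0.025 rule holds it to 0.05 (1 − 0.975² = 0.0494 if independent).

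**The case against.** The strongest reply is that the estimate is already specified. The T1 contrast from the full model gives a between-arm difference and a standard error, and dividing it by an SD from an unconditional model is a workable way to standardise. This stands. A reader might infer that no effect size can be obtained from the plan. The documents do not support that, because the contrast is there; the fault lies in how the source and denominator are worded.

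A reader might also infer that effects will be inflated by 41%. That too is unsupported. The article never mentions a residual SD, a total SD is the usual partner of bands at 0.2, 0.5 and 0.8, and the factor treats the planning correlation as the one that will be observed.

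On the interval, an unadjusted 95% CI beside a Bonferroni-tested p-value is valid for each outcome taken alone. The plan never says the CI decides significance, and it gives the analyses exploratory status. So the mismatch does not invalidate the analysis; it leaves the reader with an interval and a verdict that can disagree without explanation.

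Finally, the article condenses a fuller protocol, and naming the SD could be left to that or to an analysis plan. This carries some weight for the choice of SD. It does not cover the sentence itself, which states a source for the main estimate and states it in a way that conflicts with the neighbouring text.

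**Conclusion.** The point holds as a correction to the wording of the primary estimate. Read literally, the stated source contains no intervention effect and conflicts with the T1 contrast and with the secondary outcome section. Read generously, the standardiser is left unnamed. The consequence is modest between total SDs (about 5% in one simulated scenario) and up to a factor of 1.41 for a residual SD at correlation 0.5. It changes the reported band only for estimates close enough to a limit, but the detectable effect of about 0.55 SD lies close to one.

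The CI mismatch is real but secondary. The 14% ratio depends only on the two confidence levels, using normal multipliers. The half-widths of 0.344 and 0.393 assume no drop-out and no adjustment; the planned mixed model, with baseline in the outcome matrix and covariates, would change them.

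**What to change.** Replace the sentence with text that does three things.

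1. State that the estimate and its CI are the between-arm contrast at T1 and the CI of that contrast, both from the fitted primary mixed model.
2. Name in advance one total SD, not a residual SD, as the standardiser for the effect size. If the baseline SD is chosen, note that entry requires a complaint score in the worst fifth on either of the two primary questionnaires. This may narrow the spread of baseline scores and so raise the effect size.
3. Report 97.5% CIs for the two primary measures. If 95% CIs are also given, label them as unadjusted for the two tests.

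The cost is a reported interval 14% wider than the 95% one. Allocation, recruitment, data collection, the contrast and the test do not change. The text should be settled before outcome data are seen by arm.

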#### Secondary outcome analysis

Mixed linear models will also be used to assess the maintenance of effect across time (baseline, immediate and long-term follow-up). We will re-run the same analysis as for primary outcome, this time by including scores at long-term follow-up. Intervention effect size will be estimated using the same mixed models for each secondary and exploratory outcome measurement (Scores of ISQV and EQ-5D, the 5 overall Z-score per cognitive domain, Outcome-Questionnaire 45, PSQI, M-FIS) at both short-term follow-up (T1) and long-term follow-up (T2). As a rule, stratification factors will be included in the analyses.

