### Assignment of interventions: allocation

#### Sequence generation

Given our small sample size, and because individuals with more severe cognitive impairments might respond differently to the intervention than those with milder difficulties, we will use randomization by minimization. Although severity and interval since COVID episode are probably important prognostic factors in outcomes, we decided to achieve trial arm balance only on age, education level, gender, Centre, and severity of cognitive deficits and complaints. For cognitive deficits, scores will first be Z-scored based on normative data, and next a global Z-score calculated on all variables will be considered (sum of Z-scores divided by number of measures). A Z-score will also be calculated for both tools assessing cognitive complaints. For both these objective and subjective indices, balance will be done by Z-score range of 0.5 (e.g., Z-score from 0 to -0.50; -0.51 to -1, etc.). For age we will use 18–29; 30–39; 40–49; 50–59; 60–70. For education, we will use 4 levels: 1. primary or professional education; 2. secondary education; 3. bachelor; 4. master. In the calculation of the imbalance each arm and each prognostic factor will have the same weight. The imbalance score is calculated based on all previous allocations as well as the current participant's hypothetical allocation to each treatment. The distance measure used to calculate the imbalance score is the marginal balance. If there is no imbalance, the allocation will be completely random. If there is an imbalance, the treatment with the lowest imbalance score is chosen with a 75% probability.

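### For the five cognitive domain scores, the secondary models use baseline as a response and, in part, as a covariate, while the follow-up contrast ignores the domain's own baseline

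*Protocol article*

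**What the plan says.** Four statements in the protocol article have to be read together.

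- Primary outcome analysis, on drop-out: the mixed model will "consider the baseline data as part of the outcome matrix".
- Same section, on covariates: "objective Z-score (Z-score from 0 to -0.50; -0.51 to -1, etc.) and gender will also be included in the model as stratification factors".
- Sequence generation, on how that score is built: individual test scores are normed, then "a global Z-score calculated on all variables will be considered (sum of Z-scores divided by number of measures"). For minimisation, "balance will be done by Z-score range of 0.5". All of this uses tests taken at baseline.
- Secondary outcome analysis: effects are "estimated using the same mixed models for each secondary and exploratory outcome measurement", including "the 5 overall Z-score per cognitive domain", at both follow-ups, and "As a rule, stratification factors will be included in the analyses". No exception is stated for the cognitive outcomes.

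The covariance is described only as participant-level random intercepts and slopes nested in centre; no residual structure is given. The effect of interest is the between-arm contrast at the follow-up visit. The article does not say that the arms' baseline means are held equal.

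**The concern.** For BRIEF, MMQ and the other questionnaires, the objective band is a separate baseline variable and an ordinary covariate. For the five cognitive domain scores it is an average that contains the baseline value being modelled. It therefore explains more of the spread at baseline than at follow-up. A model that shares one residual variance across visits then carries some of the small baseline variance into the T1 standard error.

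There is also a loss of information. With baseline in the response and free baseline means in each arm, the T1 contrast (with complete data) is simply the follow-up difference adjusted for the stratification factors. The best single predictor of a follow-up domain score, its own baseline, plays no part in it.

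The stake is moderate. These are secondary outcomes, but they are the ones scored by assessors who are to be blinded (Who will be blinded), and the plan puts its weight on effect sizes and intervals.

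**Working it through.** **The plan's own figure.** The protocol states no figure for the cognitive models. Its only sensitivity figure, f = 0.137 for the primary interaction, reproduces: λ = f²·N·m/(1−ρ) = 0.137² × 130 × 2/0.5 = 9.76 on 1 and 128 df, power 0.803 at alpha 0.025. It does not bear on this point.

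**Inputs.** From the protocol: N = 130, 1:1 allocation, five domains, 0.5-wide bands. Assumed: each domain has variance 1; between-domain correlation r and retest correlation ρ as stated below; five equally weighted domains unless noted.

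**Step 1: why the variances differ by visit.** Let G be the mean of the five baseline domain scores.
- Var(G) = Cov(baseline, G) = (1 + 4r)/5
- Cov(T1, G) = (ρ + 4r)/5

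At r = 0.3, ρ = 0.6: Var(G) = 2.2/5 = 0.44 and Cov(T1, G) = 1.8/5 = 0.36.
- Residual variance at baseline: 1 − 0.44 = 0.56
- Residual variance at T1: 1 − 0.36²/0.44 = 0.71

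With G cut into 0.5-wide bands, simulation gave 0.59 at baseline, 0.72 at T1 and 0.73 at T2. So baseline is only partly accounted for by the covariate.

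**Step 2: effect on the standard error.** SE = √(4 × residual variance/130).
- Correct at T1: √(4 × 0.72/130) = 0.149
- One pooled variance over three visits: (0.59 + 0.72 + 0.73)/3 = 0.68, so SE = √(4 × 0.68/130) = 0.145
- Ratio: 0.145/0.149 = 0.97

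**Step 3: fitted models** (model SE divided by true SE; n = 40,000 rescaled to 130).

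| Covariance | Domain's share of global score | T1 | T2 |
|---|---|---|---|
| Three visits, random intercept and linear slope | one fifth | 0.95-0.97 | 1.01-1.02 |
| Three visits, random intercept and linear slope | 40-50% | 0.83-0.93 | 1.03-1.05 |
| Variances free by visit | any | 1.00 | 1.00 |

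These cover r = 0.2-0.4 and ρ = 0.5-0.75. Coverage of a 95% interval at T1 is about 94% in the first row and 90-93% in the second. A further check at r = 0.3, ρ = 0.7 with equal domains gave a T1 SE about 2% too small and a T2 SE about 1% too wide. In 600 simulated trials of N = 130 (r = 0.3, ρ = 0.6, random intercept and slope), the contrast was within 0.007 SD of zero under the null, the mean T1 SE was 0.142 against an empirical 0.148, and coverage was 0.947. Adding a band-by-time interaction does not repair the SE (about 0.96).

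**Step 4: precision left unused.** The T1 residual variance given both the band score (taken as continuous) and the domain's own baseline B is 1 − c′S⁻¹c. Here c = (ρ, Cov(T1, G)), and S has Var(B) = 1 and Var(G) = Cov(B, G).
- r = 0.3, ρ = 0.7: G only, 1 − 0.38²/0.44 = 0.672; G and B, 0.489; 27% less
- r = 0.5, ρ = 0.7: G only, 1 − 0.54²/0.60 = 0.514; G and B, 0.450; 12% less
- r = 0.6, ρ = 0.6: 0.471 in both; no gain

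With the actual bands, which carry less information than continuous G, the reduction was 15-30% at ρ = 0.7 and r = 0.3-0.5, and 0-48% over the wider range. Replacing the band by the domain's own baseline is not always a gain: the residual variance could rise by up to 25%, when between-domain correlation is close to retest. Removing the band and changing nothing else raises the SE from about 0.148 to √(4 × 1/130) = 0.175.

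**The case against.** The strongest reply is that the double use does not by itself make any interval wrong. The plan states random intercepts and slopes. With only two visits, that gives a covariance in which T1 has its own variance; simulation of this case gave SE ratios of 0.99-1.03 and type I error of 4.7-5.4%. Larger two-visit errors appear only under a random intercept alone, which is not what the plan describes. With three visits the shortfall needs a linear random slope and a common residual variance. The article states neither, and a full analysis plan may settle both. The analyses are called hypothesis-generating, no significance threshold is set for these outcomes, and the opening words of the stratification sentence leave room for an exception.

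Most of this stands. A reader might infer that baseline is fully explained by itself, that the T1 and T2 intervals are simply wrong, or that a cognitive effect will be overstated. The protocol does not support those readings: the covariate is a coarse band of an average over all tests, it is fixed before randomisation and balanced by minimisation, the contrast is unbiased, and the error depends on a covariance structure not given here. A reader might also extend the point to BRIEF and MMQ. The covariate list omits complaint severity, so there is no such overlap.

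The reply does not remove the overlap itself, which the text prescribes for these five outcomes without exception, or the unused own-baseline information.

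**Conclusion.** The point holds in limited form. For the five cognitive domain scores the stated model has baseline on both sides, in part, and the follow-up contrast does not adjust for the domain's own baseline.

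- Bias in the arm contrast: none.
- T1 standard error: about 2-5% too small with equally weighted domains and a common residual variance; up to about 17% if a domain makes up half of the global score; correct if variances differ by visit. The Neuropsychological tasks section lists many attention and executive tasks but two long-term memory tasks, so unequal shares are plausible. The article does not show how tests map to domains.
- T2 standard error: 1-5% too large with a linear random slope.
- Precision: the larger practical loss in most settings, but it shrinks to nothing when between-domain correlation equals retest.

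All sizes rest on assumed correlations. The other secondary outcomes are unaffected, because their baseline values are not in the objective Z-score.

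**What to change.** Add a sentence to Secondary outcome analysis covering the five cognitive domain scores only.

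**Preferred:** T1 and T2 are the responses, that domain's own baseline score is a covariate, and the objective Z-score band stays in as a minimisation factor. Baseline is then no longer on both sides, and the contrast gains the own-baseline information.

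**Alternative, if baseline is to remain a response so that drop-outs are retained:** leave the objective band out of these models, constrain the baseline means to be equal across arms, and allow a separate variance at each visit. All three parts are needed; removing the band alone loses precision.

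The cost is small. No new data are needed, because the baseline domain scores are already collected. The cognitive models will differ from those for the other outcomes, and under the preferred option participants with no follow-up score do not contribute.
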